#### Sample size

Simon’s two-stage design for a one-sample exact test was estimated, assuming a one-year survival rate of 0.20 or less under the null hypothesis, and 0.5 or more under the alternative, with 80% power and 5% type I error rate. A total of 17 patients will be recruited into the study (at the end of stages 1 and 2). 9 patients will be recruited into the study in the first stage. Once 9 patients have completed their 24 weeks visit, the study will stop for futility if only 2 or fewer patients have survived with the native liver. At the end of the second stage, if 7 or more patients out of the 17 enrolled have survived with native liver at 24 weeks post HMB002 treatment, this will demonstrate proof of concept. DSMB approval is required for progression to Stage 2, where the trial will continue to recruit a further 8 patients. this will be extended to 17 patients as part of the Simon two stage design if there is evidence to support continuation. A long-term follow-up period will be used to monitor safety over a 10-year period post investigational medicinal product (IMP) infusion.

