#### Outcomes

*Primary endpoints*.

Safety: Moderate to severe (including life threatening and death) adverse event occurrences due to product in 1^st^ 52 weeks post procedureTolerability: assessed by the proportion of initiated infusions where >80% of the infusion is received by the patient.Biological activity: Survival with native liver at 24 weeks post treatment.

*Secondary endpoints*.

Change in blood marker levels including haematological, biochemical and coagulationbaseline to 52 weeks post treatment.Quality of life measuresPatient survival with native liver at 52 weeks post treatmentPatient survival with transplanted or native liver at 24- and 52-weeks post treatment.

*Exploratory end points*

To assess the assay ‘Hepamorph’ which distinguishes the recipient liver cell derived proteins from the donor liver cell derived proteins using a targeted mass spectrometry approach.To analyse viability and function of microbeads which are retrieved from the intraperitoneal cavity either at laparoscopy or transplant for phenotype ex vivo.

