#### Data collection and management

*Plans for assessment and collection of outcomes*. Source documentation for the study includes, but is not limited to informed consent forms, medical records, clinical reports, laboratory reports, hospital correspondence and quality of life questionnaires. The validated PedsQL forms used in the study are PedsQL Parent (13–18 years) version 4.0, PedsQL Infant(1-12months) version 1.0, PedsQL Infant(13-24months) version 1.0, PedsQL Parent (2–4 years) version 4.0, PedsQL 5–7 Years version 4.0, PedsQL Parent (5–7 years) version 4.0, PedsQL 8–12 Years version 4.0, PedsQL Parent (8–12 years) version 4.0 and PedsQL 13–18 Years version 4.0.

*Plans to promote participant retention and complete follow-up*. Participants have the right to withdraw from the study at any time for any reason. Should a patient decide to withdraw from study, efforts will be made to explain the importance of remaining on trial follow up and seek permission to continue to allow routine follow-up data to be used for trial purposes (with parent / legal guardian consent). Patients who undergo liver transplant following IMP administration during the study period will not be withdrawn from the study but will continue to undergo monitoring and data collection.

*Data management*. A web based electronic data capture system will be designed, using the InferMed Macro 4 system. It will be hosted at a dedicated secure server within King’s college London. A full audit trial of data entry and any changes to data will be available. Over the course of the trial, the trial monitor will conduct on-site monitoring. The data entered into an electronic form should be verifiable with original source records kept at study centre. Following completion of monitoring and data cleaning of all week-52 post IMP visit data, the site PI will review all the data for each participant and provide electronic sign-off to verify that all the data are complete and correct. At this point, all data will be formally locked for analysis. Safety monitoring data collected during the long term follow up period (week 52 to 10 years post IMP) will be recorded on a separate database and locked following PI review and sign off.

At the end of the trial, all essential documentation will be archived for a minimum of 30 years in a GCP compliant archive facility. The documents that relate to IMP traceability will be retained for a minimum of 30 years and beyond the expiry date of the product.

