#### Statistical methods

*Analysis of primary endpoints*.

The number of moderate to severe adverse event occurrences due to product in 1^st^ 52 weeks post procedure will be reported.The proportion of initiated infusions where >80% of the infusion is received by the patient will be reporter.Survival with native liver at 24 weeks post treatment and 95% confidence interval will be reported as one minus the cumulative incidence of death with native liver, liver transplant being considered as competing events.

*Analysis of secondary endpoints*.

Change in blood marker levels (haematological, biochemical and coagulation) will be reported from baseline to 52 weeks post-treatment.Change in quality-of-life measures levels will be reported from baseline to 52 weeks post treatment.Survival with native liver at 52 weeks post treatment and 95% confidence interval will be reported as one minus the cumulative incidence of death with native liver, liver transplant being considered as competing events.Overall survival and 95% confidence interval at 24 weeks and 52 weeks post treatment will be estimated using the Kaplan-Meier method.

*Other reporting*.

A comprehensive report of the collected examination items will be provided according to the protocol’s schedule of assessment.

An analysis of outcomes will be conducted at stage 1 Go/No Go time point for DSMB safety review, when the 9^th^ patient has completed their 24-week post IMP study follow up.

According to the trial design, a first analysis will be conducted once 9 patients have received the proposed treatment and completed 24 weeks of follow up. If two or fewer survive with the native liver at 24 weeks after treatment then the trial will be stopped at this stage. Once 52-week follow up is completed for all 9 patients, primary and secondary endpoint will be analysed according to the protocol specification. If more than 2 survive with the native liver at 24 weeks after treatment, then recruitment will continue to a total of 17 patients (stage 2). Once 52 week follow up will be completed for all 17 patients having received the treatment, primary and secondary endpoints will be analysed according to the protocol specification.

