#### Methods for additional analyses

There are no subgroups to analyse. Calculation of time to death will consider transplantation as a competing risk.

*Methods in analysis to handle protocol non-adherence and missing data*. This is an early phase trial, so that analysis will be conducted per protocol on patients with available data. Patients with incomplete data will therefore be discarded. Patient accrual will be continued until the required number of patients with complete data is reached.

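### The formula for survival with native liver counts every transplanted child as a native-liver survivor, so it overstates the primary efficacy endpoint by the whole transplant rate

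*Protocol article*

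**What the plan says.** The Outcomes section names the biological-activity endpoint as "Survival with native liver at 24 weeks post treatment". It lists survival with either a transplanted or a native liver as a separate secondary endpoint, so a transplanted child does not meet the primary one.

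The Sample size section applies the same meaning. Stage 1 stops for futility if 2 or fewer of 9 children survive with the native liver. Proof of concept is claimed "if 7 or more patients out of the 17 enrolled have survived with native liver at 24 weeks post HMB002 treatment". Both rules are counts, and a transplanted child counts as a failure.

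The Statistical methods section then says how the endpoint will be estimated: as "one minus the cumulative incidence of death with native liver, liver transplant being considered as competing events", with a 95% confidence interval. The secondary endpoint follows the same formula: "Survival with native liver at 52 weeks post treatment and 95% confidence interval will be reported as one minus the cumulative incidence of death".

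Two further statements bear on this. Under Methods for additional analyses: "Calculation of time to death will consider transplantation as a competing risk". Under Data collection and management: "Patients who undergo liver transplant following IMP administration during the study period will not be withdrawn from the study". Transplanted children therefore stay in the analysis set, and their transplant is handled as a competing event.

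**The concern.** A cumulative incidence with a competing event gives the probability that one particular event has occurred first. Its complement is the probability that this event has not occurred first, and that includes everyone who had the competing event. Here the competing event is transplant, which is itself a failure of the endpoint. The complement therefore moves transplanted children from the failure side to the success side.

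The headline efficacy figure and its interval would describe a different quantity from the one the go/no-go and success rules count. A trial could fail its own rule and still report high native-liver survival. The secondary objective is to inform the sample size of a larger randomised trial, and that trial could be planned on the inflated figure.

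Transplant cannot be treated as a rare nuisance. The trial objectives name bridging to transplantation as an aim, and eligibility excludes only transplantation expected within 12 hours of infusion and previous transplant.

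**Working it through.** **Inputs from the protocol article**
- Endpoint: alive with native liver at 24 weeks (Outcomes).
- Estimator: 1 − CIF(death with native liver), transplant competing (Statistical methods). CIF means cumulative incidence function.
- Design: 9 then 8 children, stop at 2 or fewer of 9, success at 7 or more of 17, null rate 0.20, alternative 0.50, 80% power, 5% type I error (Sample size). That section calls 0.20 and 0.50 one-year survival rates, but the rules apply them to native-liver survival at 24 weeks, and so do I.
- Transplant rate by 24 weeks: not given. I assume a range of 10% to 60%.

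**The plan's own figure.** The design reproduces when success means alive with native liver. The probability of stopping at stage 1 under 0.20 is the sum of C(9,x)·0.2^x·0.8^(9−x) for x = 0, 1, 2:

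0.1342 + 0.3020 + 0.3020 = 0.738.

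Exact enumeration of both stages gives a type I error of 0.034 and power of 0.806. A full search confirms that this is the minimax Simon design. The counting rules are sound.

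**The estimator.** With first events classified by 24 weeks,

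P(alive with native liver) + CIF(transplant) + CIF(death with native liver) = 1.

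Hence

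1 − CIF(death with native liver) = P(alive with native liver) + CIF(transplant).

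The excess over the endpoint is CIF(transplant). It is zero only if no child is transplanted.

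**Assumed outcomes for 17 children, complete follow-up**

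| Alive, native liver | Transplanted | Dead, native liver | Plan's formula | Endpoint | 7-of-17 rule |
|---|---|---|---|---|---|
| 4 | 8 | 5 | 1 − 5/17 = 70.6% | 4/17 = 23.5% | fails |
| 3 | 7 | 7 | 1 − 7/17 = 58.8% | 3/17 = 17.6% | fails |
| 7 | 5 | 5 | 1 − 5/17 = 70.6% | 7/17 = 41.2% | met |
| 7 | 0 | 10 | 1 − 10/17 = 41.2% | 7/17 = 41.2% | met |
| 0 | 17 | 0 | 1 − 0/17 = 100% | 0/17 = 0% | fails |

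Rows 1 and 3 give the same reported figure, although one fails the rule and the other meets it. For row 1, the exact binomial 95% interval (ignoring the two-stage design) is 6.8% to 49.9% for 4/17 and 44.0% to 89.7% for 12/17. The second interval lies wholly above the null value of 20%.

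**Expected reported value when true native-liver survival is 20%** (20% plus the transplant rate)

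| Assumed transplant rate | 10% | 20% | 30% | 40% | 60% |
|---|---|---|---|---|---|
| Reported value | 30% | 40% | 50% | 60% | 80% |

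A transplant rate of 30% alone moves the reported figure from the null to the alternative.

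**Consistency check against overall survival.** A child who is transplanted and then dies before 24 weeks never enters the incidence of death with native liver, and so still counts as a success. Suppose 2 of the 8 transplanted children in row 1 die. Overall survival is (4 + 6)/17 = 10/17 = 58.8%, yet the plan would report native-liver survival of 12/17 = 70.6%. Native-liver survivors are a subset of survivors, so this result is impossible for the named endpoint.

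**The case against.** The strongest point on the other side is that no decision rests on this formula. Futility, progression and proof of concept are all worded as counts, and their error rates are as designed. This stands, and it limits the finding to the reported estimates and intervals at 24 and 52 weeks. These are nevertheless the published result for the primary efficacy endpoint.

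A second argument is that the plural at the end of the formula hints that death and transplant were both meant to be subtracted. The endpoint list suggests that the authors may have intended this. The sentence does not say it, however: it names one event of interest and one competing event, and no other part of the article subtracts transplant or defines a composite event. Reading it as censoring at transplant does not help either, because that would not estimate the endpoint.

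Third, a large discrepancy would be visible. The native-liver count must be known to apply the rule, overall survival is reported separately, and every transplant is reported as a serious adverse event. That makes the error detectable, but the formula remains wrong. It is also not certain that a later trial would be sized on this figure, only possible.

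Fourth, the size depends on a transplant rate that the article does not give. Some eligibility rules could keep it low, such as the 12-hour exclusion and the admission of children unsuitable for transplant. This stands, and so the range starts at 10%. The direction of the error does not depend on the rate.

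Finally, an unseen analysis plan might state the estimator correctly. But this is not a detail left for later: the article states a specific formula, and that formula does not match the endpoint.

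**Conclusion.** The concern holds and must be fixed. As written, the estimator does not measure survival with native liver at 24 or 52 weeks; it measures the probability of not having died with the native liver, and exceeds the endpoint by the cumulative incidence of transplant. This is an identity and needs no outside figure. Only the size is assumed: 10 to 60 percentage points over the range considered, and 47.1 points (8/17) in the example of 4 native-liver survivors, 8 transplants and 5 deaths. The Simon stopping and success rules and their error rates are unaffected as worded, so the reported estimate could contradict the trial's own decision.

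**What to change.** In the Statistical methods section, define the event as the first of death or liver transplant. Report survival with native liver at 24 and 52 weeks as one minus the cumulative incidence of that composite, which equals 1 − CIF(death with native liver) − CIF(transplant), with the 95% confidence interval for the same quantity. With complete follow-up to the time point, this is the proportion alive with native liver and agrees with the Simon count.

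Report the two cumulative incidences separately as components. The competing-risk sentence under Methods for additional analyses can then stay, if it is stated to refer to those components.

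The cost is two changed sentences, one for each time point. No further data are needed, because death and transplant are already collected. The reported figure will be lower whenever any child is transplanted.

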#### Secondary objective

To establish proof of concept of the transplantation of microbeads made from the optimum combination of modified alginate, MSCs and hepatocytes. To inform the sample size and confidence intervals to design a larger randomized clinical trial.

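### The Kaplan-Meier interval for overall survival is zero-width or undefined at n = 9 or 17 if no child dies, and its plain and log versions can be too narrow when some do

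*Protocol article*

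**What the plan says.** Under Statistical methods, the analysis of secondary endpoints reads: "Overall survival and 95% confidence interval at 24 weeks and 52 weeks post treatment will be estimated using the Kaplan-Meier method". No variance formula, transformation or rule for zero deaths is named. The endpoint (Outcomes) counts a child as alive with either a native or a transplanted liver.

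The analysis set is small by design. It is 17 children if both stages run. After a stop at stage 1 it is 9: "Once 52-week follow up is completed for all 9 patients, primary and secondary endpoint will be analysed according to the protocol specification".

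Two other passages settle censoring. Under Data collection and management, transplanted children "will not be withdrawn from the study but will continue to undergo monitoring and data collection". Under Methods for additional analyses, "Patients with incomplete data will therefore be discarded", and accrual goes on until the required number have complete data.

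The Secondary objective includes: "To inform the sample size and confidence intervals to design a larger randomized clinical trial".

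**The concern.** With complete follow-up the Kaplan-Meier estimate at 24 or 52 weeks is an ordinary proportion, so the method adds nothing to the point estimate. It does bring a large-sample interval, which is used here on 9 or 17 children. That interval has no usable form when all children survive. Some versions are also too short at high survival even when deaths occur.

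Bridging to transplantation is part of the trial objective, and overall survival is where a child alive after transplant counts directly as a survivor. A zero-width interval would claim certainty from a handful of children, and a missing one would leave the planners of the randomised trial with nothing to use.

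**Working it through.** **Inputs.** n = 17 or 9, 95% confidence, no censoring (sections cited above). True overall survival (OS) is an assumption, because the protocol gives none. The rates under Sample size ("one-year survival rate of 0.20 or less under the null hypothesis, and 0.5 or more under the alternative") feed decision rules on native-liver survival and do not fix overall survival. The protocol states no figure for this interval, so there is none to reproduce.

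**Step 1: what the interval becomes.** Without censoring, p̂ = x/n and Greenwood's variance is p̂(1 − p̂)/n. The plain interval is p̂ ± 1.96·√[p̂(1 − p̂)/n]. The log, log-log, logit and arcsine versions transform the same quantity.

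**Step 2: no deaths.** At x = n the variance is 0. Plain and log give 100% to 100%; log-log, logit and arcsine are undefined. The exact lower limit is 0.025^(1/n):
- 17/17: 0.025^(1/17) = 0.805, so 80.5% to 100%.
- 9/9: 0.025^(1/9) = 0.664, so 66.4% to 100%.

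The chance of no deaths is OS^n:

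| OS | n = 17 | n = 9 |
|---|---|---|
| 80% | 2.3% | 13.4% |
| 85% | 6.3% | 23.2% |
| 90% | 16.7% | 38.7% |

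The n = 9 column is unconditional. A final analysis at n = 9 requires at most 2 of 9 alive with the native liver. With native-liver survival πN and survival after transplant πT = OS − πN, the joint chance of a stop and no deaths is Σ C(9,k)·πN^k·πT^(9−k), k = 0 to 2.
- OS 90%, πN = 0.5: 0.4⁹ + 9(0.5)(0.4⁸) + 36(0.25)(0.4⁷) = 0.018. The stop has probability 0.090, so the chance given a stop is 20%.
- OS 90%, πN = 0.2: joint 0.263, stop 0.738, so 36%.

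**Step 3: deaths present.** For 15/17, p̂ = 0.882 and SE = √(0.882 × 0.118/17) = 0.078. The plain interval is 0.882 ± 0.153, that is 73% to 100% after capping. Exact is 64% to 98%.

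Coverage at n = 17, OS 80%, adds the binomial probabilities of the outcomes whose interval contains 0.80:
- plain covers x = 10 to 15: 0.871
- log covers x = 9 to 15: 0.879
- log-log covers x = 11 to 16: 0.940
- exact covers x = 10 to 16: 0.967

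The plain and log versions lose 16/17 (probability 17 × 0.8¹⁶ × 0.2 = 0.096), because their lower limits there are 82.9% and 83.6%. Given at least one death, they still cover only 0.89 and 0.90.

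**Step 4: the log-log version.** With one or two deaths it is at least as wide as exact:

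| Alive | log-log | exact |
|---|---|---|
| 16/17 | 65.0–99.1% | 71.3–99.9% |
| 15/17 | 60.6–96.9% | 63.6–98.5% |
| 8/9 | 43.3–98.4% | 51.8–99.7% |

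With three deaths (14/17) the two widths nearly agree: 54.7–93.9% against 56.6–96.2%. At n = 17, log-log coverage is 0.969, 0.957 and 0.952 at OS 50%, 70% and 75%. At OS 90% it is 0.811, but 0.973 given at least one death.

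**The case against.** The strongest reply is that the protocol names only Kaplan-Meier. Greenwood, the transformation and a zero-event rule are details for the analysis plan, which is not shown. Some intervals built on Kaplan-Meier do not collapse: the beta product procedure is one, and a likelihood-ratio interval gives 89.3% to 100% at 17/17. This stands in part, since the wording does not exclude a sound interval. But choosing among the five usual transformations does not help when nobody dies, and the likelihood-ratio version still falls to 82.5% coverage at n = 17 for true survival between 0.70 and 0.99.

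A second reply is that the damaging region is assumed. The Introduction stresses high mortality without transplantation, and children unsuitable for transplant can be enrolled. At OS 70% or 75% the chance of no deaths at n = 17 is only 0.2% or 0.8%. This stands, and it limits the size of the point.

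A reader might infer that the interval is too narrow at high survival whichever transformation is used. The figures do not support that. Log-log is wider than exact at 16/17, 15/17 and 8/9. Most of the low coverage near 90% is the no-death outcome scored as a miss: given at least one death, plain, log and log-log at n = 17 cover 0.99, 1.00 and 0.97.

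A reader might also infer that this interval is a trial objective in itself. The Secondary objective speaks of informing a later trial's sample size and intervals and does not single out overall survival. Nor is overall survival the only analysis that leaves transplanted children out of the failures: the written native-liver estimator, one minus the incidence of death with native liver, does so too.

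**Conclusion.** The point holds in a limited form. If no child dies, any usual Kaplan-Meier interval is zero-width or undefined. At n = 17 the chance of this is about 2% to 17% for overall survival of 80% to 90%. At n = 9 it is 13% to 39% unconditionally; after a futility stop it depends on native-liver survival (20% or 36% in the two cases shown at 90%). Separately, the plain and log versions can under-cover with deaths present, most clearly at n = 17 and 80% survival. Log-log is adequate at n = 17 up to about 75% survival, and its shortfall above that is mainly the no-death case.

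This rests on complete follow-up, which the protocol's own rules imply, and on an assumed overall survival. It concerns a secondary endpoint. The stage 1 rule and the final success rule use counts of children alive with the native liver and are unaffected.

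**What to change.** In Statistical methods, state that overall survival at 24 and 52 weeks will be reported as x/n with a Clopper-Pearson exact 95% interval, and that the Kaplan-Meier curve is for display. Add that if any child is censored before the time point, a small-sample survival interval such as the beta product confidence procedure will be used.

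This takes a sentence or two and needs no extra patients, visits or data. The cost is a conservative interval, with coverage of about 0.97 to 0.99 at the high survival rates considered here.
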